### 1.2 Transvamic-oil (cannabinoid-based medicine oil)

Transvamic-oil is produced by the Transvaal pharmacy as a compounded medication (*magistrale bereiding*) and prescribed to patients with refractory symptoms, of which pain is the most prevalent indication. CBM-oil prescriptions have been filled out over 100,000 times to patients in the Netherlands between 2015 and 2020 . Since their appearance on the market 52 adverse events related to sublingually administered CBMs (of which 1 was serious: hypoglycemia) have been reported to the center for pharmacovigilance (LAREB). Activities such as driving vehicles or using dangerous apparatus can be impaired in the acute phase after administering CBMs containing both THC and CBD, such as through delayed reaction times. A recent study highlighted that after a single administration of 13.75mg THC and CBD, which was vaporized and inhaled, the resulting impairments did not exceed 240 minutes. Additionally, a placebo-controlled crossover study using an oromucosal THC:CBD spray in varying compositions, observed the largest decrease in subjective wakefulness at 3 hours post administration.

In general, short-term use of Transvamic-like drugs increases the risk for non-serious adverse events 1.86 times, of which dizziness is the most frequently reported . The side-effect profile however is described as acceptable for clinical practice. Detectable plasma

THC levels after oromucosal absorption are reached at 30-45 minutes and maximum concentration at 2-3 hours. Increasing dose tolerance to therapeutic effects has not been observed in Transvamic-like drugs.

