### 6.4 Summary of known and potential risks and benefits

Sublingually administered TransvamiX-like drugs comprising THC and CBD are generally well tolerated. The most common treatment related adverse events are dizziness, nausea and fatigue.

Please see *D1\_Investigators Brochure* Chapter 5.2 (Safety and Efficacy).

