## 6.6 Dosages, dosage modifications and method of administration

Transvamic and placebo are administered sublingually using a 1 millilitre dosing syringe. All participants will follow the predetermined titration scheme (*Table 2*). The titration will be stopped at the onset of side-effects (as reported by the participant), and the dose administered reduced by one day in the titration scheme. This will be called the sub-side effect threshold maintenance dose.

This achieved dose will be maintained for the remaining intervention period until day 14 is completed for each intervention (Transvamic and placebo). Both placebo and IMP (Transvamic) will undergo the same titration scheme.

The maximum dose is 0.75ml/day Transvamic or placebo (divided between 4 separate administrations).

For additional information please see *D1\_Investigators Brochure* chapter 5.3.1.

| Table 2: Titration Scheme                                 |           |          |           |            | Total   | Total THC | Total CBD |
|------------------------------------------------------------------|-----------|----------|-----------|------------|---------|-----------|-----------|
| Transvamic (100mg/mL THC & 50mg/mL CBD) & Placebo |           |          |           |            | (ml)    | (mg)      | (mg)      |
| Day                                                              | 6AM – 9AM | 11AM-2PM | 4PM – 7PM | 9PM – 12AM |         |           |           |
| 1                                                                | -         | -        | -         | 0,05 ml    | 0,05 ml | 5         | 2,5       |
| 2                                                                | -         | -        | -         | 0,05 ml    | 0,05 ml | 5         | 2,5       |
| 3                                                                | 0,05 ml   | -        | -         | 0,05 ml    | 0,1 ml  | 10        | 5         |
| 4                                                                | 0,05 ml   | -        | 0,05 ml   | 0,05 ml    | 0,15 ml | 15        | 7,5       |

|    |         |         |         |         |         |    |      |
|----|---------|---------|---------|---------|---------|----|------|
| 5  | 0,05 ml | 0,05 ml | 0,05 ml | 0,05 ml | 0,2 ml  | 20 | 10   |
| 6  | 0,05 ml | 0,05 ml | 0,05 ml | 0,1 ml  | 0,25 ml | 25 | 12,5 |
| 7  | 0,1 ml  | 0,05 ml | 0,05 ml | 0,1 ml  | 0,3 ml  | 30 | 15   |
| 8  | 0,1 ml  | 0,05 ml | 0,1 ml  | 0,1 ml  | 0,35 ml | 35 | 17,5 |

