### 8.3.1 Daily participant logbook completed by participants.

Participants will complete a logbook consisting of 3 parts each day in the evening (table 1) throughout the study period during which the participant received either Transvamic or placebo:

- Visual analog scales for pain and pruritus (VAS [no pain] 0-100 [worst pain/pruritus imaginable] units). These will be completed in the evening. Participants will be asked to complete VAS pain/pruritus retrospectively about the same day, subdivided into 3 timepoints in the day (*morning, afternoon and evening [or now]*).  
The periods of completion are as follows: Firstly, for baseline measurements (day -8 to -1) followed by Transvamic and placebo interventions (days 1 - 14 and 29 – 42).

- The titration scheme will be visualised and a checkbox ticked by the participant indicating the day of titration that was completed.
- Side effects will be reported following a multiple choice list\*, and the burden of the noted side effect indicated using numeric rating scales (NRS [not burdensome] 0-10 [extremely burdensome])
- Use of breakthrough medication or changes in analgesic medication recorded by participant.

\* Multiple choice list of side effects are categorized (in Dutch):

1. High gevoel (een vrolijke opgewekte stemming die langzaam overgaat in een tevreden gevoel van kalmte en rust).
2. Loomheid
3. Honger
4. Intensere beleving van kleuren en/of geluiden
5. Verlies van gevoel voor tijd en/of plaats
6. Sombere en/of angstige stemming
7. Rusteloosheid en/of slapeloosheid
8. Waanvoorstellingen
9. Versnelde hartslag
10. Duizeligheid
11. Warm of koud gevoel in handen en voeten
12. Rode branderige ogen
13. Spierverslapping
14. Droge mond
15. Anders, namelijk.....

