### 9.2 AEs, SAEs and SUSARs

#### 9.2.1 Adverse events (AEs)

Adverse events are defined as any undesirable experience occurring to a subject during the study, whether or not considered related to Transvamic or placebo. All adverse events reported spontaneously by the subject or observed by the investigator or his staff will be recorded.

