### 13.2 Synthesis

CBMs in the Netherlands have gained special status on the Dutch prescription pharmaceutical market and is prescribed when other registered treatments are deemed ineffective or futile. Evidence produced by Dutch local academic institutions is lacking. The production of pharmaceutical grade medical cannabis is approved by the Ministry of Health of the Netherlands, and the extraction process forming the oil composition follows GMP guidelines regulated by the government board of health inspection. Variations in the composition of cannabinoids of the CBM-oil used in this study have been readily available on prescription since 2015 and no serious or life-threatening events have been reported to the ministry of health. The study drug Transvamix (THC 100mg/mL (10%), CBD 50mg/mL (5%)), is being developed under GMP regulations for the application in clinical studies. Phase I and II have not been required for dispensation to patients in the Dutch healthcare setting.

The safety profile of this combination of cannabinoids is well understood, however this is the first time that Transvamix is being used in a clinical study on patients with epidermolysis bullosa (EB). Although this is a rare disease, the mechanisms of top-down symptoms (pain) in EB overlap other painful diseases which have been studied in the context of CBM trials. This study is designed to safely monitor patients throughout, as well as minimize burden of participation. Participants are allowed to use breakthrough and co-medications so as to not lead to additional patient suffering during participation.

In summary this explorative study will reciprocate current clinical practice in order to measure the lay a foundation for future studies in this field. The controlled study setting allows for both the CBM intervention to be supervised as well as closely monitor (possible) changes in patient outcomes, and brain connectivity. This objective data will cornerstone the directions of future clinical research in EB and CBMs.

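### The daily side-effect checklist has no item for nausea, which the protocol counts among the three commonest reactions, so nausea is at risk of being under-counted

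*Protocol*

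**What the plan says.** Section 6.4 names the reactions to be expected: "The most common treatment related adverse events are dizziness, nausea and fatigue".

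Section 8.3.1 describes the evening logbook. There, "Side effects will be reported following a multiple choice list", and each effect noted is scored for burden from 0 to 10. The list, given in Dutch, has 14 named effects and a fifteenth open entry, "15. Anders, namelijk" (other, namely). Dizziness is on it: "10. Duizeligheid". Item 2, *Loomheid* (lethargy), is close to fatigue. No item names nausea.

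The logbook supplies a stated objective. Section 2.3 wants the frequency and burden of adverse events during titration. Section 8.1.2 makes the number and kind of events, with the burden of each, a secondary endpoint. Section 10.2.1 reports them by frequency and burden for placebo and for Transvamix.

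There is a second route into the safety data. Section 9.2.1 says: "All adverse events reported spontaneously by the subject or observed by the investigator or his staff will be recorded".

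**The concern.** The checklist is the measuring instrument for the adverse-event endpoint. An effect with a tick box is asked about every evening. An effect without one has to be recalled, judged worth mentioning and written out by the participant. If the two kinds of effect are then tabulated together, their frequencies are not measured on the same footing.

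Here the unprompted effect is one that the protocol itself expects to be common, while red eyes, intensified colours or sounds and muscle relaxation, none of which Section 6.4 names as common, each have a prompt. A table built from this logbook could show nausea as rarer than those effects partly because of how the question was asked. Section 9.5 sets up a DSMB to follow adverse events because basic safety and tolerability data are said to be lacking, so this profile is one of the things the trial is meant to supply. A later analysis plan cannot repair the gap, because it lies in what is collected.

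**Working it through.** The protocol gives no figure for side-effect capture, so there is none to reproduce. The check is a comparison of lists.

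**Step 1. Expected reactions (Section 6.4) against the 15 logbook entries (Section 8.3.1).**

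| Reaction in Section 6.4 | Named logbook item | Prompted? |
|---|---|---|
| Dizziness | Item 10, *Duizeligheid* | Yes |
| Fatigue | Item 2, *Loomheid* (near equivalent) | Approximately |
| Nausea | None; open item 15 only | No |

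Two of three have a named item and one of three does not. None of the other named items (high feeling, hunger, altered senses, disorientation, low or anxious mood, restlessness, delusions, fast heartbeat, warm or cold extremities, red eyes, muscle relaxation, dry mouth) could reasonably be read as nausea.

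**Step 2. Routes by which nausea can still enter the data.**

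- Open item 15. It belongs to the list, so a burden score can be attached, but the participant must volunteer the effect.
- Spontaneous report or staff observation (Section 9.2.1). This is also unprompted. Dosing is at home (Table 1), which leaves staff few occasions to observe it, and Section 9.2.1 attaches no burden score.

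Nausea is thus reportable but never asked about.

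**Step 3. What unequal prompting does to the endpoint.** Let *p_T* and *p_P* be the true proportions with nausea on Transvamix and on placebo, and let *c* be the fraction captured without a prompt, relative to the capture with one.

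- Observed proportions: *c·p_T* and *c·p_P*.
- Difference between treatments: *c·(p_T − p_P)*, shrunk by the factor *c*.
- Ratio between treatments: *c·p_T / c·p_P = p_T / p_P*, unchanged if *c* is the same in both periods.
- Nausea compared with a prompted effect: lowered by the factor *c*.

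With *c* below 1, the absolute frequency of nausea, its rank among the side effects and its absolute difference from placebo are all understated. With *c* equal to 1, nothing is lost. The protocol gives neither *c* nor an expected rate of nausea, so no number can be put on the effect.

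**The case against.** The strongest reply is that nothing is lost. The list ends in an open field, and all spontaneously reported or observed events must be recorded anyway. The same list also serves both periods, so a ratio of Transvamix to placebo is unaffected if capture is equal in each. All of this is correct. It means that under-counting is a risk and not an established fact. It does not remove the unequal elicitation, since both remaining routes depend on the participant volunteering the effect or on staff noticing it. The endpoint also reports frequencies and burden for each treatment, not only a ratio.

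Three stronger readings are tempting, and the protocol does not support them.

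- **Titration.** A reader might infer that nausea would fail to stop dose escalation. Section 6.6 says: "The titration will be stopped at the onset of side-effects (as reported by the participant". That rule is not tied to the checklist, so a participant who reports nausea meets it as written. Whether the missing item changes what participants regard as a side effect is conjecture.
- **Hypoglycaemia.** Section 1.2 mentions 52 reported events with sublingual products, "of which 1 was serious: hypoglycemia", and one might ask for a prompt for that too. It is a single report, the protocol does not call it common, it is a diagnosis more than a felt symptom, and a serious case would go through the reporting of serious adverse events in Section 9.2.2.
- **A contradiction on safety.** Section 13.2 says that "no serious or life-threatening events have been reported to the ministry of health". This sits uneasily with Section 1.2, but the recipients differ (the ministry in one, the pharmacovigilance centre in the other) and the range of products may differ. It is not a strict contradiction and has no bearing on the checklist.

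It can also be said that prompting is not neutral, because an added item may itself raise reporting. That stands, and is counted below as a cost.

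**Conclusion.** The point holds in a limited form. The protocol names three commonest reactions and prompts for two of them. Nausea is left to the open field and to spontaneous reporting, so it is elicited less completely than the listed effects and is at risk of being under-counted in the adverse-event frequency and burden endpoint. The omission itself is certain, since it can be read off the list. The consequence rests on one assumption, that an unprompted effect is reported less fully than a prompted one, and its size cannot be derived from the document.

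The primary endpoint is untouched. This is an inexpensive improvement to the instrument behind a secondary objective. The relation between Sections 1.2 and 13.2 is a separate, minor matter of wording.

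**What to change.** Add nausea to the checklist in Section 8.3.1 as a named item with the same 0-10 burden score as the others, in the same form in both intervention periods. Keep the open field for anything else. This brings Sections 6.4 and 8.3.1 into line.

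The cost is one more item in the online logbook and a moment per entry. Prompting may slightly raise the number of side effects reported, on placebo as well as on Transvamix. Because participant-reported side effects also bear on titration and so on the dose reached, the item should be in place before the first participant starts, so that everyone answers the same list. No dose or clinical rule needs to change for this.

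Separately, add a sentence in Section 13.2 that reconciles its summary with the serious report in Section 1.2, stating to whom each set of events was reported and which products it covers.

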### 8.3.2 Surveys completed by participants

The short form McGill Pain Questionnaire (SF-MPQ2) and pain self-efficacy questionnaires (PSEQ) will be completed 3 times. Firstly at baseline (day -1), followed by the last day of both Transvaxim and placebo interventions (days 14 and 42).

*The douleur neuropathique 4 (DN-4), central sensitisation index (CSI), hospital anxiety and depression survey (HADS) and pain catastrophizing scale (PCS) are additional surveys that will be completed at baseline (day -1) only.*

### 8.3.3 Functional Magnetic Resonance Imaging

During eligibility screening for the study, the MRI safety form will be completed and checked by the research clinician.

The fMRI scans will be repeated on three occasions at the cognitive neuroscience centre, UMCG. Firstly, the baseline will be obtained prior to intervention (pre-dose measurement). The second fMRI scan will take place on day 14. The third fMRI

scan on day 42.

Each scanning procedure consists of two parts:

1. T1 weighted anatomical scan (10 minutes)
2. Resting state scan (10 minutes – participants are instructed to close eyes, not fall asleep and let their minds roam freely. Heart rate and breathing rate will be recorded continuously).

#### **8.3.4 Urine THC-COOH Toxicology**

Urine samples will be collected and analyzed at the department of clinical toxicology UMCG. During the study, urine toxicology will be assessed for THC-COOH at 2 time points: On day 14 and 42 (on the last day of Transvamic and placebo intervention). Participants will collect first-urine in the morning (before morning administration) and take this to the study clinical visit, to be collected by the research clinician.

Toxicology results will not be revealed until the end of the study period, after the data analysis for the primary outcome is complete.

#### **8.3.5 Follow-up Structured Interview**

Participants who have completed participation, or who have dropped out (and have given consent for regular follow-up) will be contacted by telephone or video conferencing by the research clinician. The interview will consist of 3 parts:

1. General perspectives on participation (related to recruitment and study design)
2. General perspectives on interventions (related to Transvamic and placebo).
3. General and specific feedback for future studies pertaining to CBMs as interventions and/or EB patients.

Directly following the structured interview, participants will be sent via email an automated researcher-blinded question on the order of interventions received (the responses will be unblinded after statistical analysis of the study is completed). The options are: I) Transvamic → Placebo, II) Placebo → Transvamic, III) I don't know.

### **8.4 Withdrawal of individual subjects**

Subjects can leave the study at any time for any reason if they wish to do so without any consequences. The investigator can decide to withdraw a subject from the study for urgent medical reasons.

**8.5 Replacement of individual subjects after withdrawal**

In case of participant or research physician decided withdrawal, the recruitment will continue until n=16 have been enrolled and completed participation in the study.

**8.6 Follow-up of subjects withdrawn from treatment**

The researchers will ask the subject who has withdrawn to clarify whether they wish to withdraw from all components of the trial or allow for the standard follow-up to take place at 14 days post end of study (which was consented to when commencing participation).

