### **9.4 Follow-up of adverse events**

All AEs will be followed until they have abated, or until a stable situation has been reached. Depending on the event, follow up may require additional tests or medical procedures as indicated, and/or referral to the general physician or a medical specialist. SAEs need to be reported till end of study within the Netherlands, as defined in the protocol

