### **12.4 Temporary halt and (prematurely) end of study report**

The sponsor will notify the accredited METC and the competent authority of the end of the study within a period of 90 days. The end of the study is defined as the last patient's last visit.

The sponsor will notify the METC immediately of a temporary halt of the study, including the reason of such an action.

In case the study is ended prematurely, the sponsor will notify the accredited METC and the competent authority within 15 days, including the reasons for the premature termination.

Within one year after the end of the study, the investigator/sponsor will submit a final study report with the results of the study, including any publications/abstracts of the study, to the accredited METC and the Competent Authority.

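### Section 8.6 does not separate stopping study drug from leaving the study, so no primary-outcome score is provided for after a participant stops

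*Protocol*

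**What the plan says.** The heading of section 8.6 concerns subjects withdrawn from treatment, but its text treats the person simply as withdrawn. The choice put to them is to leave the trial entirely or to "allow for the standard follow-up to take place at 14 days post end of study". No third option is offered.

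Section 8.3.5 describes the follow-up: "Participants who have completed participation, or who have dropped out (and have given consent for regular follow-up) will be contacted by telephone or video conferencing". The interview covers views on taking part, views on the interventions, and "General and specific feedback for future studies pertaining to CBMs as interventions and/or EB patients". An emailed question on the order of treatments follows. Table 1 places the interview on day 55 and adds that it also covers events. No pain questionnaire is listed.

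The primary outcome is the SF-MPQ2 unpleasantness score (8.1.1, 10.1). Section 8.3.2 schedules this questionnaire at baseline, "followed by the last day of both Transvaxim and placebo interventions (days 14 and 42"). No assessment at early stopping is described. Section 8.5 continues recruitment until 16 participants have completed. Section 10.1 plans paired or independent t-tests or non-parametric tests, plus mixed effects models that are meant to deal with missing data.

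On timing, 12.4 states: "The end of the study is defined as the last patient's last visit".

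**The concern.** Whether a participant takes the drug and whether the participant stays under observation are separate matters. Section 8.6 joins them. A person who stops the oil but would gladly fill in a questionnaire at home has no stated way to do so, and the next thing the protocol arranges is an interview without the primary instrument.

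Combined with replacement of withdrawals, following the plan yields a data set of people who got through both periods. If stopping is related to treatment, the Transvamix-placebo contrast then describes those who could stay on treatment, which is narrower than the primary objective in 2.2. A relation to treatment is plausible: section 1.2 cites a 1.86-fold risk of non-serious adverse events with similar drugs. The loss occurs at data collection, so an analysis plan written later cannot undo it.

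**Working it through.** **1. Is power the issue?** Section 4.4 uses a mean of 5.76 and SD of 1.45, 80% power and alpha 0.05, and states 9 participants for a 30% reduction and 5 for a 50% reduction.
- Target differences: 5.76 × 0.30 = 1.728 points and 5.76 × 0.50 = 2.88 points.
- Two-sided paired t-test, with SD of the within-participant difference = 1.45 × √(2(1 − ρ)), where ρ is the within-participant correlation. The protocol does not give ρ, so it is assumed.
- ρ = 0.5 (SD 1.45): 8 and 5 participants. ρ = 0.4 (SD 1.59): 9 and 5, matching the stated figures.
- With 16 completers, power for the 30% target is 88% at ρ = 0 (SD 2.05) and 99% at ρ = 0.5.

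Sixteen completers are enough on these inputs. The question is bias, not power.

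**2. What each participant contributes to the primary outcome under 8.6 and 8.3.2**

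| Participant | Day -1 | Day 14 | Day 42 |
|---|---|---|---|
| Completes both periods | yes | yes | yes |
| Stops in period 1 and leaves | yes | not provided for | not provided for |
| Stops in period 2 and leaves | yes | yes | not provided for |

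A paired test drops both kinds of stopper. In a mixed model, the second-period stopper's day 14 score still adds some between-participant information. The first-period stopper has only a baseline score and says nothing about either treatment.

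**3. Illustration of the gap between completers and all enrolled.** Assumptions, none of them from the protocol: k stoppers are replaced, so 16 + k are enrolled; completers gain 30% over placebo; stoppers gain nothing. Effect over all enrolled = (16 × 30% + k × 0) / (16 + k).

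| k | Enrolled | Share stopping | Effect over all enrolled | In points (1.728 × 16 / enrolled) |
|---|---|---|---|---|
| 1 | 17 | 5.9% | 28.2% | 1.63 |
| 2 | 18 | 11.1% | 26.7% | 1.54 |
| 3 | 19 | 15.8% | 25.3% | 1.46 |
| 4 | 20 | 20.0% | 24.0% | 1.38 |

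The points column borrows the general pain mean from 4.4, because the protocol gives no mean for unpleasantness.

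**4. Timing of the follow-up**
- 8.6: 14 days after the end of study.
- 12.4: the end of study is the last patient's last visit, a trial-level event not tied to any one participant.
- Table 1: day 55, on the participant's own calendar. Fourteen days after day 42 would be 42 + 14 = day 56.

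The three do not give one date. None is counted from the day a participant stops.

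**The case against.** Several objections are sound and limit the point.

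- **The protocol does not forbid a later SF-MPQ2.** A reader might infer that the score can never be obtained after stopping. The text supports only that it is not provided for.
- **Side effects are not expected to lead to stopping.** Under 6.6, a participant with side effects goes back one step in the titration scheme and holds that dose to the end of the period, so the day 14 or 42 questionnaire is kept. Stopping remains possible, since 8.4 lets anyone leave at any time, but the protocol does not present it as the usual course.
- **Stoppers do not all lack primary data.** A reader might take the 11% to 20% shares above as people with no score on treatment. That holds only if every stopper stops in period 1. Daily VAS entries up to stopping are also kept, though the VAS is a secondary outcome.
- **Safety follow-up is not absent.** Because 9.4 says "SAEs need to be reported till end of study within the Netherlands", a reader might infer that the interview falls after reporting has closed. That needs the 12.4 definition, written for notifying authorities, to override day 55 in Table 1. Day 55 suggests that 8.6 means the participant's own end of participation. Section 9.4 also follows every adverse event until it abates or stabilises, 9.5 sets up a DSMB, and Table 1 includes events in the interview.
- **The trial is explorative, and much of the completer selection comes from 8.5.** This is true and keeps the point modest. But 8.6 is where scores from willing stoppers could be kept, and without them the effect of replacement cannot be examined.

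**Conclusion.** The point holds as a data-collection gap. Section 8.6 merges stopping drug with leaving the study, and no primary score is provided for after stopping. With replacement to 16 completers, the primary comparison becomes one of completers. The mixed model can use partial records but cannot supply scores that were never collected.

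The size of any bias is unknown. In the illustration with 2 to 4 stoppers, the 30% effect in completers exceeds the all-enrolled effect by 3.3 to 6.0 percentage points. This rests on assumed stopper counts and assumed zero benefit in stoppers, and is not a forecast.

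The timing statements in 8.6, 12.4 and Table 1 are inconsistent, which is a drafting matter to reconcile. The documents do not support a finding that adverse-event follow-up is missing. Overall this is an inexpensive improvement, not a flaw that undermines the trial.

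**What to change.** - Amend 8.6 to distinguish a participant who stops study drug from one who withdraws from the study.
- Let those who stop the drug but agree to stay complete the online SF-MPQ2, PSEQ and VAS at stopping and again on the scheduled day 14 or 42. Flag these scores as off-drug.
- State that these scores enter the mixed model or a sensitivity analysis.
- Reconcile 8.6, 12.4 and Table 1 so that they agree on when the follow-up takes place.

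Cost: changes to protocol and consent wording, and a slight burden on the few who stop. Table 1 allows 20 minutes for the two questionnaires and 10 minutes for the logbook that holds the VAS, so two rounds take at most 2 × (20 + 10) = 60 minutes, done at home with no extra visit. Some scores will be off-drug and must be labelled and interpreted as such.
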